## Objective

The objective of this pilot study is to assess the feasibility, and potential effectiveness, of the Move More @ Work intervention designed to encourage staff to take 1–2-min opportunities to move after every 30 min of prolonged sitting over the work day. An opportunity to move is defined as greater than 1 min of light to moderate activity involving repeated movement of some kind (e.g., brisk walking, body weight resistance exercises, or moving through a series of stretches). The study will inform if progress to a full effectiveness trial is warranted. The specific aims of this study are the following:
Evaluate the recruitment rate of participants into the study, and retention of those participants through the intervention and post-intervention period.Qualitatively examine the acceptability of the Move More @ Work intervention to participants, workplace management, and where possible, employees not involved in the intervention but working in close proximity to those that were.Evaluate the extent to which Move More @ Work changes the number of opportunities to move taken over the work day and the extent of participant adherence to the intervention.Examine the potential effects of Move More @ Work on Cardio-Metabolic Risk score (an estimated risk based on waist circumference, blood pressure, fasting glucose, triglycerides and High Density Lipoprotein [HDL] cholesterol), musculoskeletal health, psychological well-being, and perceptions of work productivity.Use the findings to refine the intervention and inform the development of a subsequent effectiveness trial of the Move More @ Work intervention.Estimate the sample size required in a subsequent effectiveness trial evaluating the intervention.

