### Move More @ Work intervention

The aim of this 12-week intervention is to encourage participants to perform 1–2 min of activity after every 30 min of continuous sitting throughout their workday. The intervention contains an individual behaviour change component delivered by a Move More @ Work Coach and a workplace culture component. The Behaviour Change Wheel [18] and the associated COM-B model and TDF were used in the design of the intervention along with research evidence of behaviour change strategies important to support reduction in sedentary behaviour [13] and our work investigating facilitators and barriers to performing regular activity breaks [15]. The specific intervention components and their mapping to the COM-B model and TDF are shown in Table 2.

**Table 2 Tab2:** Links between the COM-B model, TDF domains, intervention functions, and behaviour change techniques used in the Move More @ Work Intervention

COM-B model component and definition of the barrier/motivator influencing change		TDF domains	Intervention functions	Behaviour change techniques	Description of intervention strategy
Capability	*Psychological* A lack of knowledge of why prolonged sitting is harmful to health and benefits of incorporating regular movement.	*Knowledge* Increase knowledge of health risks to prolonged sitting (even when regularly physically active) and benefits of reduced sitting time. *Beliefs about consequences* Create expectancy that positive outcomes will occur with reduced sitting.	Education, persuasion	• Information on health consequences • Credible source	• Information on health consequences discussed by the Move More @ Work coach (MMWC) and in study booklet provided to participants.
	*Psychological* A lack of awareness of how sedentary the individual currently is.	*Knowledge* Increase awareness of how sedentary the individual currently is.	Education, persuasion	• Feedback on behaviour • Discrepancy between current behaviour and goal	• Participant booklet displays individualised pre-intervention activity patterns at work and expected behaviour during intervention. • Consultation with MMWC discusses discrepancy between current and expected behaviour and elicits participant’s feelings about discrepancy to encourage motivation to change.

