Briefly, discuss current evidence around sitting as a health hazard, and the health benefits associated with performing regular short bouts of movement throughout the day.Discuss and demonstrate where necessary, examples of physical activities that meet the intensity and duration required of an opportunity to move (for example, walking up and down stairs or along a corridor; repeatedly standing up from the chair and sitting back down; body weight resistance exercises such as squats, calf raises). Links to online videos demonstrating these specific movements will be provided in the study booklet.Discuss the participant’s profile of the time they spent sitting and being active at work collected from the pre-intervention accelerometer data. The coach will highlight the discrepancies between current sedentary time and the expected behaviour if participants take an opportunity to move every 30 min.Develop an individualised action and barrier-coping plan [26]. The action plan involves participants specifying exactly what activities they will perform (and would easily fit into their work context), when they will do them (e.g., may have different activities at different times of the day), and where (e.g., in the office, on the stairs). The barrier-coping plan involves participants identifying potential barriers that they may face when implementing this plan and putting strategies in place to overcome those barriers. A laminated card will be provided for the participant to record their action and barrier-coping plan each week. They will be encouraged to place this card within eyesight of their workstation to assist with self-monitoring.Provide participants with a laminated chart to record each opportunity to move that was performed each work day. At the end of each day, a section on the chart will prompt participants to self-reflect on how they are feeling.Discuss which external electronic prompt the participant would like to use as a reminder to take their opportunities to move (e.g., an outlook calendar reminder — available on a PC or Mac, or the computer announcing the time every 30 min — Mac only). The coach will then help the participant set these prompts up on their computer.

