ActiGraph data will be saved in 15-s epochs and data from both the ActiGraph and ActivPAL will be uploaded into Stata for processing. Non-wear time and hours spent at work will be identified based on times reported in the wear time diary. Days will only be considered valid if: wear time during waking hours is ≥ 10 h, and total wear time is ≥ 20 h. A participant’s data will only be included in analysis if it contains more than three workdays of valid data. Using the ActiGraph data, time spent sedentary will be classified as < 150 cpm using the *y*-axis [28]. Time spent in light and moderate-to-vigorous physical activity will be identified using a threshold of 150 to 1951 cpm and at least 1952, respectively, using the *y*-axis thresholds [29]. Time spent asleep will be identified using the Sadeh algorithm [30] constrained by the bedtimes reported in the wear time diary. The activPAL data will be used to identify time spend sitting, standing, and stepping that will be presented in parallel to the ActiGraph data. An opportunity to move will be defined as an increase in counts per minute to over 1000 cpm (ActiGraph data), when the participant is not seated (activPAL data) that is sustained for more than a minute (adjustments will be made if any participants have issues with mobility). Our previous work [31] indicates that the 1000 cpm threshold is associated with the intensity of activity shown in laboratory studies to produce clinically meaningful reductions in postprandial glucose and insulin concentrations. To avoid clusters of activity being identified as multiple breaks, at least 15 min of sedentary time must have been accumulated between opportunities to move. Total and work time spent in moderate-to-vigorous physical activity, light activity, sedentary behaviour, and sleep will be identified.

Self-reported adherence to the intervention will also be collected. Participants will record the number of opportunities to move taken each work day and will send the weekly record to the research team by email at the start of the following week.

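### As written, the accelerometer rule for an opportunity to move would not count the repeated chair-stands that participants are coached to do

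*Protocol article*

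**What the plan says.** The primary outcome (Protocol article, Pilot study primary outcome) is the change in the mean number of opportunities to move per workday, from T1 and T2 to T3 and T4.

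The counting rule is under Change in physical activity behaviour. Its intensity part reads "An opportunity to move will be defined as an increase in counts per minute to over 1000 cpm (ActiGraph data". Its posture and duration part continues "when the participant is not seated (activPAL data) that is sustained for more than a minute". One relaxation is offered: "adjustments will be made if any participants have issues with mobility". The rule also needs at least 15 min of accumulated sedentary time between counted bouts.

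Under Move more @ work coach consultation, the coach discusses and demonstrates "examples of physical activities that meet the intensity and duration required of an opportunity to move". The examples include "repeatedly standing up from the chair and sitting back down; body weight resistance exercises such as squats, calf raises". The Objective section defines an opportunity to move as "greater than 1 min of light to moderate activity involving repeated movement of some kind" and sets no condition on posture.

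Participants also keep their own daily tally, described as self-reported adherence. The progression criteria require at least half of the sample to average at least 8 opportunities at the end of the intervention. They do not say whether the device count or the tally is meant.

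**The concern.** The article tells participants that chair-stands qualify, then fixes a counting rule whose posture condition chair-stands break at every repetition. A participant could do exactly what the coach demonstrated and have it scored as nothing.

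The timing turns this into a bias as well as a loss of precision. The consultation follows the pre-intervention period and uses its accelerometer data, so coached chair-stands appear mainly at T3 and T4. An activity that is rare before coaching and uncounted after it lowers the post-intervention count while leaving the baseline almost untouched. The estimated change is then too small.

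There is also a problem of interpretation. The participant's tally would include chair-stands and the device count would not. A gap between the two could mean over-reporting or non-detection, and the pilot could not tell which.

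**Working it through.** **1. The two passages side by side**

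- Coach consultation: chair-stands are listed among activities said to meet the required intensity and duration.
- Counting rule: over 1000 cpm, not seated on the activPAL, for more than a minute.
- Exceptions: mobility problems only.
- A set of chair-stands alternates between seated and not seated, so the posture condition lapses at each repetition. With no stated tolerance for brief sits, no unbroken non-seated period longer than a minute arises within the set.
- The other coached examples (stairs, corridor walking, squats, calf raises) are not seated and raise no posture conflict.

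**2. The plan's own sample size, as a base for scale**

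Inputs from Sample size: SD 3, within-person correlation 0.5, difference 3, alpha 0.05 (taken as two-sided), power 90%, cluster size 5, ICC 0.8.

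- SD of change = 3 × √(2 × (1 − 0.5)) = 3.
- n = ((1.960 + 1.282) × 3 / 3)² = 10.5, rounded up to 11.
- Design effect = 1 + (5 − 1) × 0.8 = 4.2.
- 11 × 4.2 = 46.2, rounded up to 47, as stated.
- 47 × 1.2 = 56.4, rounded up to 57, as stated.

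The conflict in step 1 does not depend on these figures.

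**3. Illustration of scale**

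The documents give no share of chair-stands, so the shares below are assumptions. Let m be the share of the added opportunities that go uncounted, with the SD of change held at 3. The recorded change is 3 × (1 − m). Power at 47 is Φ(√(47/4.2) × 3(1 − m)/3 − 1.960), where √(47/4.2) = 3.345.

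- m = 0: change 3.0, power 92%.
- m = 10%: change 2.7, power 85%.
- m = 20%: change 2.4, power 76%.
- m = 33%: change 2.0, power 61%.

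**4. The progression criterion, if it uses the device count**

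Let k be the share of all end-of-intervention opportunities that go uncounted. Registering 8 then takes 8/(1 − k) true opportunities: 8.9 at k = 10%, 10 at 20% and 11.9 at 33%. If the criterion uses the participants' tally, this step does not apply.

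**The case against.** The strongest reply is that this is processing detail. A condensed article need not say how the activPAL classifies sits of a few seconds or whether short interruptions are tolerated, and a fuller document may say so. The duration phrase can also be read as attached to the rise in counts, with posture a concurrent condition. Chair-stands are only one of several coached examples. This reply stands against any claim that chair-stands can never be counted. It does not remove the conflict: the article states a posture condition, names one exception, and coaches an activity that falls outside both. Under either reading of the phrase, the seated moments still break the posture condition unless a tolerance is added.

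A reader might infer three further faults, which the documents do not support.

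- **Duration.** The intervention aims to "encourage participants to perform 1–2 min of activity after every 30 min of continuous sitting", so a bout of exactly one minute would comply but not count. That is a boundary mismatch in the wording of the instruction. The rule itself agrees with the Objective, which also requires longer than a minute. It is true that "ActiGraph data will be saved in 15-s epochs", but nothing says that five full epochs (75 s) must exceed the threshold. The loss of 37.5% of bouts that such a rule would give, for durations uniform on 60 to 120 s, rests on two assumptions from outside the article. A four-epoch rule under the same model would still lose 12.5%, and every bout of exactly 60 s.
- **Intensity.** The 1000 cpm threshold lies within the article's light band of 150 to 1951 cpm and has a stated metabolic rationale. Allowing light activity does not mean that every light count must qualify, so a second count from 150 cpm would be a preference.
- **Progression.** Failure of the criterion cannot be asserted, because the article does not say which count it uses.

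**Conclusion.** The point holds in a limited form. Read literally, the counting rule does not score chair-stands, which the article itself coaches as qualifying, and the two sections must be reconciled. Because coaching starts after T2, any undercount falls mainly on T3 and T4 and biases the primary change toward zero.

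The direction of the bias rests on two assumptions: that chair-stands are uncommon as work breaks before coaching, and that the processing has no unstated tolerance for brief sits. The size cannot be derived from the documents, and the figures for 10% to 33% uncounted show scale only. The effect on the threshold of 8 is conditional on its being a device count. The article also does not show that chair-stands exceed 1000 cpm at the hip beyond saying that the coached examples meet the required intensity. If they do not, the posture condition is not the only barrier.

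**What to change.** Change the processing rule and leave the intervention as it is.

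- Under Change in physical activity behaviour, state that a run of consecutive sit-stand transitions on the activPAL, with ActiGraph counts over 1000 cpm for more than a minute, is treated as one non-seated bout.
- Apply this identically at T1, T2, T3 and T4.
- Keep the 1000 cpm threshold, the requirement of more than a minute and the 15-min separation between bouts.
- In the progression criteria, state whether the count of 8 is device-measured or self-reported.

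The cost is some extra processing code and two sentences of text, with no change to data collection. A few more incidental bouts will be counted, under the same rule at every wave.

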#### Cardio-metabolic risk score

Cardio-metabolic risk assessment will be undertaken at pre-intervention T2. This assessment comprises measures of waist circumference, weight, height, blood pressure, triglycerides, HDL, and fasting glucose. Waist circumference will be measured to the nearest 0.1 cm with a steel measuring tape at the midpoint between the lowest rib and the iliac crest. Weight will be measured to the nearest 0.1 kg with the participant wearing light clothing and no shoes using calibrated body weight scales. Height will be measured to the nearest 0.1 cm, without shoes, with the individual looking straight ahead (Frankfort plane), using a calibrated stadiometer. All anthropometric measurements will be taken in duplicate, with a third measurement taken if the first two differ by more than 0.5 units. Blood pressure will be measured via a digital blood pressure monitor (OMRON HEM-907; Omron Healthcare, Japan) using the right arm and appropriately sized cuff. Participants will rest in a seated position for 15 min prior to having three measurements taken at 1-min intervals. Fasting blood samples will be collected at the Department of Human Nutrition Research Clinic in the morning by a trained phlebotomist for the analysis of glucose and lipids (triglycerides, HDL cholesterol). Samples will be centrifuged within an hour of collection and plasma stored at – 80 °C until analysis, which will be conducted in the Department of Human Nutrition Diabetes and Lipids Laboratory. Lipid and glucose concentrations will be measured using glycerol phosphate oxidase and hexokinase enzymatic methods, respectively, on a Cobas C 311 analyser.

The overall cardio-metabolic risk score will then be calculated by first log10 transforming and normalising (mean/SD) the relevant biomarkers and then taking a weighted average of their values: 1/5 waist circumference + 1/5 triglycerides − 1/5 HDL + 1/5 fasting glucose + 1/5 mean of systolic and diastolic blood pressure. This method has been used in previous research [32].

*Musculoskeletal health* will be assessed using the Standardised Nordic Questionnaire [33]. This measures musculoskeletal problems in nine body areas (neck, shoulder, upper back, elbow, wrist, lower back, hip, knee, and ankle). Participants respond either yes or no to whether they have had experienced any trouble in each body area and, if so, how much pain was experienced on a scale of 1 to 10. A lower score signifies better musculoskeletal health. Similar to Dunstan et al. [34], the wording will be modified to refer to the last 7 days and last 3 months (instead of 12 months).

*Psychological well-being* will be assessed using the Positive and Negative Affect Schedule — short form (PANAS) [35]. This scale assesses two sub-scales: negative affect and positive affect. Participants report on a 5-point Likert-type from 1 (never) to 5 (always) the extent to which they generally feel each of the 10 items. Lower scores on the negative affect subscale and higher scores on the positive affect subscale represent better psychological well-being.

*Work engagement* will be assessed using the Utrecht Work Engagement Scale 9 [36] which comprises three sub-scales: vigour, dedication, and absorption. Participants record on a 7-point Likert scale (0 [never] to 6 [always, every day]) how frequently they have had a particular feeling described in each item. Higher scores represent greater work engagement.

*Occupational fatigue* will be assessed using the 11-item Need for Recovery Scale [37]. The scale assesses the extent to which work tasks induce a need to recuperate from work induced effort. Participants report with a yes or no to each of 11 items. The sum of the items scored as ‘no’, is multiplied by 100 and divided by 11 (the total number of scale items) resulting in an overall score between 0 and 100. A higher score reflects a greater need for recovery and increased short-term work-related fatigue.

*Impact of health on work* will be assessed using the Work Limitations Questionnaire — Short Form [38]. Participants rate their level of difficulty (or ability) to perform in eight areas of work in the past two weeks (e.g., to concentrate on work, speak with people, handle the workload, and finish on time) on a scale capturing the percentage of time they have met the specific work demand (‘all of the time (100%)’, ‘most of the time’, ‘some of the time (about 50%)’, ‘a slight bit of the time’, ‘none of the time (0%)’ and ‘does not apply to my job’). The eight items comprise four work limitation sub-scales: time management, physical demands, mental and interpersonal, and output demands. Responses are converted to percentages to create a score ranging from 0 to 100 for each subscale. Higher scores reflect greater difficulty in being able to perform their work.

### Data analysis

Descriptive statistics will be used to assess the feasibility outcomes of time taken to recruit and retention of participants across the intervention. Intervention acceptability will be assessed through analysis of participant interviews. They will be open-coded, examining for common themes in relation to acceptability and usefulness of the intervention. They will then be axially coded, investigating the relationships between the themes and the similarities and differences in individuals’ reporting and experiences of those themes [39].

The primary and secondary outcomes of the pilot study will be assessed using mixed effects regression models, where the independent variables in the model will be: time since baseline, pre-/post-intervention (dummy variable), and a time by pre-/post-intervention interaction variable. The immediate effect of the intervention will be represented by the regression coefficient of the pre-/post-intervention variable, with the regression coefficient of the interaction term representing the difference in change in the outcome over time. Because this study examines within-person changes, only participants with data at T1, T2, and T3 will be included in the primary analyses, using an intention-to-treat approach. Office clusters will be included as a random effect. Where appropriate, the Stata command ‘itsa’ (for interrupted time series analysis) will be used. Mean changes in outcomes with 95% CI will be reported. To illustrate the results of the pilot study and assist in interpretation, line graphs will be generated. No interim analysis is planned for the trial. All quantitative statistical analysis will be carried out using Stata (StataCorp, Texas).

To estimate sample sizes for a future effectiveness trial, standard deviations of the change in health outcomes (e.g., body weight, blood pressure, and lipids) between T2 and T3 will be calculated. Estimates of intraclass correlation coefficients (from office clusters) will also be used to estimate the design effect if the future trial is planned to be a cluster randomised controlled trial [40].

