#### Pilot study primary outcome

The primary outcome is workday physical activity behaviour, specifically, the change in the mean number of opportunities to move taken during a workday from the pre-intervention period (T1 and T2) to the end of the intervention (T3) and post-intervention (T4) periods. An estimated change will be calculated, along with an estimate of the within-person variability, which can then be used in sample size calculations for future studies.

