### Sample size

From a feasibility study perspective, a formal sample size calculation is not required. However, for the pilot study component, one stated aim is to investigate changes in the number of opportunities to move taken over the work day (by comparing data from the pre-intervention to post-intervention periods) and the extent of participant adherence to the intervention. Consequently, using the standard deviation in the number of opportunities to move observed in previous research [5], our sample size calculation indicate that 47 participants from approximately 10 different offices will provide 90% power to detect a difference of three opportunities to move between pre-intervention and completion of the intervention or post-intervention periods to an alpha level of 0.05. This assumes that the within-person correlation in activity breaks is 0.5 and the standard deviation is 3. To account for office clusters a design effect of 4.2 was used (using an average cluster size of *n* = 5 and a strong ICC of 0.8). Allowing for a drop-out of rate of ~ 20%, 57 participants will be recruited. Having this stated sample size will also allow us to investigate the feasibility of achieving our target recruitment goal.

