### Retention

Participants will receive a weekly email from the research team, which aims to promote adherence to the intervention and retention in the study. Follow-up data will be collected from all available participants irrespective of their compliance to the intervention.

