### Criteria to indicate that a future effectiveness trial is feasible

Drawing on suggested criteria [23, 41] decisions on whether to proceed to an effectiveness trial is warranted will be determined on the basis of (1) meeting stated recruitment (57 participants within 1 month) and retention (retaining 80% of participants from pre-intervention to post-intervention follow-up) targets; (2) participants expressing that the conduct of the intervention was acceptable, that the components contained with the intervention were useful, and that any implementation barriers experienced by participants can be overcome; (3) that at least 50% of the sample recorded an average of at least 8 (half of the possible 16 in an eight hour day) opportunities to move at the end of the intervention; and (4) within and between estimates of variation in health indicators of interest can be observed, to inform the appropriate sample size calculation for an effectiveness trial.

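### The primary analysis set requires data at T1, T2 and T3, which makes it a complete-case set rather than intention-to-treat, and the planned mixed model does not need that restriction

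*Protocol article*

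**What the plan says.** In Data analysis, the article sets the model first: "The primary and secondary outcomes of the pilot study will be assessed using mixed effects regression models". The fixed terms are time since baseline, a pre/post indicator and their interaction, with office as a random effect. It then sets the analysis population. The reason offered is "Because this study examines within-person changes", and the rule is that "only participants with data at T1, T2, and T3 will be included in the primary analyses, using an intention-to-treat approach".

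Three other places bear on this:

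- **Retention:** "Follow-up data will be collected from all available participants irrespective of their compliance to the intervention".
- **Change in physical activity behaviour:** a wear-time filter is added, "A participant’s data will only be included in analysis if it contains more than three workdays of valid data".
- **Pilot study secondary outcomes and Cardio-metabolic risk score:** the pre-intervention assessment of this score is at T2 only. Pilot study outcomes likewise exempts blood-related measures from the four-visit schedule.

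The Sample size section allows for about 20% drop-out, and the retention target is 80%. Loss of about one participant in five is thus the plan's own working expectation.

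**The concern.** An intention-to-treat set is fixed by who entered the study, not by what was later observed. Requiring T3 removes everyone lost during the intervention. In a 12-week behaviour-change study, those people may well differ from the ones who stayed.

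The stated reason does not support the rule. A likelihood-based mixed model estimates within-person change from whatever visits each person has. The rule also discards people who do carry information on change: someone with valid T2, T3 and T4 data is dropped for a missing T1.

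Nor can the rule apply literally to every outcome that it covers. If it is applied outcome by outcome, nobody qualifies for the cardio-metabolic score, because that score has no T1 value.

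At stake are the population that the estimated change describes, some precision and, depending on how its denominator is read, the third progression criterion.

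**Working it through.** **Inputs from the Sample size section.** SD 3, within-person correlation 0.5, difference 3, alpha 0.05 (taken as two-sided), power 90%, cluster size 5, ICC 0.8, drop-out about 20%, 57 recruited.

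**1. Reproducing the plan's figure.** The plan says that "47 participants from approximately 10 different offices will provide 90% power to detect a difference of three opportunities to move".
- SD of change = 3 × √(2 × (1 − 0.5)) = 3.
- n = (1.96 + 1.2816)² × (3/3)² = 10.51, rounded up to 11.
- Design effect = 1 + (5 − 1) × 0.8 = 4.2.
- 11 × 4.2 = 46.2, rounded up to 47, as stated.
- 47 × 1.2 = 56.4, rounded up to 57, as stated.

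The same formula gives power at any analysed number n: Φ(√(n/4.2) − 1.96).

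**2. Number analysed at the planned drop-out.** 57 × 0.8 = 45.6, with power Φ(√(45.6/4.2) − 1.96) = 0.91. Drop-out alone costs almost nothing.

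**3. Adding the wear-time filter.** The article gives no rate of valid records. Assume a proportion v valid at each visit, independently across visits, among the 80% who remain.
- With the rule, all three visits must be valid: 57 × 0.8 × v³.
- Without it, those informative on change to T3 have a valid T3 and at least one valid pre-intervention visit: 57 × 0.8 × v × (1 − (1 − v)²).

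| v (assumed) | Analysed with rule | Power | Informative without rule | Power |
|---|---|---|---|---|
| 0.95 | 39.1 | 0.86 | 43.2 | 0.89 |
| 0.90 | 33.2 | 0.80 | 40.6 | 0.87 |
| 0.85 | 28.0 | 0.73 | 37.9 | 0.85 |

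At v = 0.90 the rule accounts for the step from about 0.87 to about 0.80. The rest of the shortfall is missing T3 data, which no model recovers.

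**4. Size of a possible bias (assumed values).** Let a share m leave, stayers change by 3 and leavers change by L. The mean over all participants is (1 − m) × 3 + m × L.
- m = 0.2: L = 0, 1, 2 gives 2.4, 2.6, 2.8. Completers overstate by 0.6, 0.4, 0.2.
- L = 0: m = 0.1 to 0.3 gives an overstatement of 0.3 to 0.9.

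**5. Direction of bias.** A simulation used SD 3, correlation 0.5, a true mean change of 3 and about 20% lost at T3 (150 runs of 400 participants).

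| Who tends to leave | Completers | Mixed model, all available data |
|---|---|---|
| Those with low observed pre-intervention activity | 2.85 | 3.01 |
| Those with a poor individual response (individual changes with SD 1.5) | 3.28 | 3.28 |

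The completers' estimate is too low in the first case and too high in the second. Using all available data repairs the first case and leaves the second unchanged.

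**6. Progression criterion 3.** It asks that "at least 50% of the sample recorded an average of at least 8" opportunities to move at the end of the intervention. If the sample means about 45 with T3 data, half is 23 people; if it means all 57, half is 29. A count of 23 to 28 would pass on one reading and fail on the other.

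**The case against.** Several defences have force.

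**The label may have meant regardless of adherence.** The Retention section supports that reading, and non-compliers with T3 data do stay in the set. There is also no randomised comparison to protect. This explains the wording, but a set that requires T3 still leaves out everyone lost earlier.

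**The model has a pre-intervention time trend, so T1 and T2 are both useful.** That is true. But the trend is estimated from the group, so a person with only one of the two visits need not be removed.

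**Sensitivity analyses for missing data may be in an analysis plan that is not shown.** This is accepted, and their absence from the article is not part of the point. The analysis set and its label are fixed in the article itself.

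A reader might also infer three stronger things that the article does not support.

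- **That the effect will be overstated.** The direction depends on why people leave, and one plausible mechanism gives an understatement. The largest gap at 20% loss, 0.6, needs every leaver to change by exactly zero.
- **That the study becomes underpowered.** At the planned drop-out, power is about 91%. The fall to about 33 analysed rests on an assumed validity rate, and removing the rule recovers only part of it.
- **That the progression proportion is inflated.** Criterion 3 refers to the sample, not to the primary analysis set, and retention is judged separately under criterion 1, so leavers are not hidden from the decision. What stands is that the denominator is not stated.

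**Conclusion.** The rule is wrong as written: it defines a complete-case set, calls it intention-to-treat, and rests on a reason that the chosen model makes unnecessary. It also drops people with usable T3 data who miss only T1 or T2, and it does not fit the cardio-metabolic score.

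The consequences are moderate. The estimate applies to those who stayed and may err either way, by 0.2 to 0.6 in the illustration with 20% loss and leavers changing by 0 to 2. The loss of power caused by the rule itself is about 7 percentage points if 90% of records are valid at each visit, and negligible if drop-out is the only loss. None of the four progression criteria depends on the estimated effect or its significance. This should be fixed, but it does not undermine the pilot.

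**What to change.** - Make the primary analysis the likelihood-based mixed model on all enrolled participants with at least one valid pre-intervention measurement. Use all available visits and state the missing-at-random assumption.
- Drop the intention-to-treat label, or replace it with a plain description of the set.
- Keep participants with T1, T2 and T3 data as a sensitivity analysis, and word it so that outcomes first measured at T2 are covered.
- Add a missing-not-at-random sensitivity analysis, for example with missing T3 set to the participant's pre-intervention mean. It is needed because all-available data do not remove bias when poor responders leave.
- For progression criterion 3, state the denominator, and also report the proportion among all enrolled with missing T3 counted as not reaching 8. This belongs beside the criterion rather than in place of it, since it scores a device failure at T3 as a behavioural failure. With 20% missing, it would require 0.5/0.8 = 62.5% of those measured.

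The cost is wording and a few extra model runs. The reported effect may change slightly.
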